### Ethical considerations

The study protocol complies with the Declaration of Helsinki and has been granted approval from the Medical Ethics Committee of Maastricht University/Academic Hospital Maastricht. (NL33281.068.10/MEC10-3-074). The study is registered in the Dutch trial register (NTR2663).

### Study protocol

#### Training of nursing home physicians

Nursing home physicians (NHP) at each healthcare organisations (four per site) will participate in the study. The physicians will receive a refresher course, from a cardiologist specialising in HF at the Maastricht University Medical Centre, regarding diagnosing HF and performing a structured physical examination. Training will consist of an introduction about signs and symptoms of HF followed by bed-side teaching (3 hours) and a session and lecture about ECG findings in relation to HF (2 hours). The NHP will subsequently visit the University Medical Centre’s out patient HF clinic to refresh their knowledge and practise diagnostic skills related to HF (3 hours).

#### Assessment of heart failure

After training the NHP will start assessing the participants. During the assessment, the study NHP will perform the anamnesis and the physical examination. To ensure that no prior probability of HF is taken into account during the history taking and physical examination, the NHP will not have access to pre-existing information about the residents, with the exception of their name and date of birth. Two research nurses and a NHP/researcher, who will be responsible for gathering data from the medical records and the questionnaires, will record the ECG and take blood samples for the measurement of the NT-pro BNP marker. The ECG will be interpreted by the same study NHP who executed the examination. A qualified (fellow) cardiologist will record the echocardiogram on site, using a mobile echo device with recording capabilities. The entire assessment will be carried out on site in the participating nursing homes.

#### Diagnosis of heart failure

The final diagnosis of HF will be based on all the data collected and will be made by an expert team of two cardiologists and a geriatrician using the definition of HF from the guidelines of the European Society of Cardiology 2008 [2].

To diagnose HF, data will be collected from actual clinical examinations (including history, physical examination, ECG, cardiac markers and echocardiogram) and from the patients’ records (past medical history and medication).

At the end of the assessment all residents will be categorized in one of the following groups:

1.No HF

2. HF, no previous history

3. HF, already known (either overt HF with signs and symptoms or re-compensated HF)

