**Methods/design:**

Nursing home residents in the southern part of the Netherlands, aged over 65 years and receiving long-term somatic or psychogeriatric care will be included in the study. A panel of two cardiologists and a geriatrician will diagnose heart failure based on data collected from actual clinical examinations (including history, physical examination, ECG, cardiac markers and echocardiography), patient records and questionnaires. Care dependency will be measured using the Care Dependency Scale. To measure the quality of life of the participating residents, the Qualidem will be used for psychogeriatric residents and the SF-12 and VAS for somatic residents.

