## Background

Heart failure (HF) is a highly prevalent chronic disease in older persons. Its prevalence increases with age reaching 15–20% in those aged over 80 years [1]. According to current guidelines [2], HF is stated as a clinical syndrome characterized by the presence of symptoms and typical signs of HF and objective evidence of a structural and/or functional abnormality of the heart, usually illustrated by echocardiography [2]. Accurate diagnosis of the presence and aetiology of HF is important given its crucial influence on therapy. However, signs and symptoms of HF in older persons are often obscured, due to physical limitations or the unreliability of clinical history due to dementia [3]. In addition, signs of HF, such as fatigue or dyspnoea, are often attributed to the normal ageing process. Besides, symptoms are often non-specific and can be attributed to other common diseases in older persons such as venous insufficiency or obesity [4]. The diagnosis of HF is especially challenging if co-morbidities are present that share common symptoms of HF are present such as COPD and venous insufficiency [5].

This implicates that the diagnosis of HF is particularly difficult in older persons and nursing home residents. The latter represent a specific group, involving very frail and disabled elderly persons with chronic somatic diseases or progressive dementia, both often being complicated by co-morbidities [6]. The prevalence of HF in nursing home residents is estimated to be 20–25% [3,7]. Furthermore, HF in this specific group is likely to be underdiagnosed, due to the lack of knowledge regarding adequate diagnosis and treatment of HF in this population. This counts the more because nursing home residents are often excluded from clinical and epidemiological studies.

It is well known that HF is accompanied by a high patient and economic burden [8]. HF patients are often re-admitted to hospital, mainly due to periodic episodes of clinical deterioration [9]. In the Netherlands, as well as other Western countries cardiovascular diseases (including HF) account for the highest hospitalisation rate, resulting in high financial costs [10,11].

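### The article is inconsistent on whether questionnaires feed the heart failure diagnosis; read literally, two statements admit the outcome scales of research question 3

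*Protocol article*

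**What the plan says.** The protocol article describes the basis of the panel's diagnosis in several places.

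- **Abstract, Methods/design.** The sources are the clinical examinations, "ECG, cardiac markers and echocardiography), patient records and questionnaires".
- **Diagnosis of heart failure, first sentence.** "The final diagnosis of HF will be based on all the data collected". The panel is one geriatrician with two cardiologists, and it reaches its diagnosis "using the definition of HF from the guidelines of the European Society of Cardiology 2008".
- **Diagnosis of heart failure, next paragraph.** "To diagnose HF, data will be collected from actual clinical examinations (including history, physical examination, ECG, cardiac markers and echocardiogram". The only record data named alongside these are earlier illnesses and drug treatment. Questionnaires are not in this list.
- **Table 1.** The block for diagnosing heart failure holds history, physical examination, ECG, NT-pro BNP, echocardiography and record data (blood test, X-thorax). Qualidem, SF-12, VAS and the CDS have their own rows further down.
- **Assessment of heart failure.** The research nurses and a physician-researcher are the ones "who will be responsible for gathering data from the medical records and the questionnaires". The examining physician is kept from pre-existing information about the resident. Nothing comparable is stated for the panel.

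Research question 3, at the end of the Background, asks how heart failure relates to care dependency and quality of life.

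**The concern.** In research question 3, heart failure is the exposure and the CDS, SF-12, VAS and Qualidem scores are the outcomes. If the people who assign the exposure can see the outcomes, the outcomes can leak into the exposure. A low CDS score might tip an unclear case towards heart failure, or towards another explanation. The estimated association would then partly reflect the panel's reasoning, and adjustment in the analysis could not reliably undo that.

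Unclear cases are to be expected. The Background says that signs and symptoms in this population are often masked or non-specific and that diagnosis is particularly difficult. It also links heart failure symptoms to greater care dependency, so a dependency score is the kind of information a panel might lean on.

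**Working it through.** **1. What the word questionnaires can refer to.** The article does not define it.

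- Physical examination and clinical history puts the cardiac history on a client record file made for the study.
- Assessment of heart failure names medical records and questionnaires as two separate sources, gathered by research staff, while the examining physician takes the history.
- The instruments named beyond the clinical work-up are the CDS, SF-12, VAS, Qualidem and MMSE. The first four are the outcomes of research question 3.

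The natural referent is therefore the outcome scales, though a structured history form is not ruled out.

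**2. The statements side by side.**

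| Place | Questionnaires as a diagnostic input? |
|---|---|
| Abstract, Methods/design | Yes, named |
| Diagnosis of heart failure, first sentence | Yes, if read literally |
| Diagnosis of heart failure, next paragraph | Not listed |
| Table 1, heart failure block | Not listed |

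The abstract cannot be squared with the list. The first sentence can be, but only if it is read as the data collected for diagnosis.

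**3. What limits the influence of the scores.** The Background describes the syndrome by the "presence of symptoms and typical signs of HF and objective evidence of a structural and/or functional abnormality of the heart". No dependency or quality-of-life score is part of that, so the scores could act only where the panel has to use judgement.

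**4. Size, as an illustration only.** The documents state no figure for this. The inputs taken from Sample size calculation are a prevalence of 0.20 and 1000 residents. The plan's 983 reproduces as 1.96² × 0.20 × 0.80 / 0.025² = 983.4, with 0.025 read as the half-width of the confidence interval. The point does not depend on that figure.

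Assumptions that are not in the documents:
- there is no true association, and the score is roughly normal;
- a share of residents is borderline;
- the more dependent half of them is always called heart failure and the other half never.

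The mean of each half of a standard normal distribution is ∓√(2/π) = ∓0.798 SD. All other residents average zero.

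*Heart failure total held at 200 against 800:*
- 10% borderline (50 residents each way): 0.798 × 50/200 + 0.798 × 50/800 = 0.1995 + 0.0499 = 0.25 SD.
- 5% borderline (25 each way): 0.798 × 25/200 + 0.798 × 25/800 = 0.0998 + 0.0249 = 0.12 SD.

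*Prevalence of 20% applied to the non-borderline residents only, so that the total rises:*
- 10%: heart failure share 0.05 + 0.90 × 0.20 = 0.23; 0.798 × 0.05/0.23 + 0.798 × 0.05/0.77 = 0.173 + 0.052 = 0.225 SD.
- 5%: share 0.025 + 0.95 × 0.20 = 0.215; 0.798 × 0.025/0.215 + 0.798 × 0.025/0.785 = 0.093 + 0.025 = 0.12 SD.
- 2%: share 0.01 + 0.98 × 0.20 = 0.206; 0.798 × 0.01/0.206 + 0.798 × 0.01/0.794 = 0.039 + 0.010 = 0.05 SD.
- 0%: no bias.

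Partial sorting, or leanings in both directions that partly cancel, would give smaller values.

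**The case against.** The strongest reply is that the specific text should govern the general. The paragraph straight after the broad sentence lists what is collected for diagnosis, Table 1 separates the diagnostic items from the outcome scales, and the Measurements section describes them under different headings. On that reading, the broad sentence means all the diagnostic data, and the abstract has one loosely chosen word. This is a fair reading and may well be what was intended. It does not remove the conflict with the abstract, which positively names questionnaires as a source.

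A second reply is that the article condenses a fuller protocol, and that the content of the panel's dossier and the blinding of adjudicators are commonly left to that document. This stands as far as it goes: the missing blinding statement is not an error by itself. The point here is that two statements about the diagnostic inputs disagree.

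A third reply concerns size. The borderline share is assumed, complete one-way sorting is extreme, and the article sets no power against which to judge a difference. All of this stands, so the figures show only what could happen.

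A reader might go further and infer that the panel is given the outcome scores, or that they decide the diagnosis. The documents support neither. No section says that the panel receives them, and the diagnosis is tied to a guideline definition that, as described, contains no such score.

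**Conclusion.** The point holds as an inconsistency with a plausible route to bias. The abstract admits questionnaires as a diagnostic input, and the first sentence of Diagnosis of heart failure does so if taken literally. That section's own list and Table 1 do not. Because the likely referent is the set of outcome scales for research question 3, incorporation of outcome information into the heart failure label is not excluded in unclear cases. It could create or distort the associations with care dependency and quality of life.

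The size cannot be derived from the documents and may be near zero. The range of 0.12 to 0.25 SD requires 5 to 10% borderline residents, complete sorting in one direction, 20% prevalence and no true association. It is an upper-end illustration and not an estimate. The correction is worth making because it is almost free before the panel meets and hard to replace afterwards.

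**What to change.** 1. Reword the abstract and the first sentence of Diagnosis of heart failure to match that section's list and the heart failure block of Table 1. The inputs would be history, physical examination, ECG, NT-pro BNP, echocardiogram, past medical history and medication, plus blood tests and X-thorax where available. The last two should stay in, because Table 1 lists them for the diagnosis.
2. Add one sentence stating that CDS, SF-12, VAS and Qualidem results are withheld from the panel until each resident's diagnosis is locked.

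If the full protocol already says this, only the article's wording needs to be aligned. The cost is two small edits and leaving four forms out of the panel's dossier. Data collection and sample size do not change.

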## Measurements

The data required to answer the research questions are listed in Table 1.

**Table 1 T1:** Overview of data collection

**Variable**		**Measurement**	**Specified**
Clinical characteristics			
	Age	Years	
	Sex	Male, female	
	Diagnosis at admission	Data from medical record	ICD-10
	Co-morbidity	Data from medical record	ICD-10
	Medication	Medication description	Non-cardiac medication
	Cognitive impairment		MMSE
Heart failure		Diagnosis of HF	
		- History	*Suffers from:*
			Dyspnoea on exertion, rest dyspnoea, paroxysmal nocturnal dyspnoea
			Palpitations/irregular heartbeat, leg oedema, orthopnoea, fatigue, increased weight
			*Is known to have:*
			Hypertension, myocardial infarction, cardiac arrhythmia, angina pectoris (chest pain)/coronary artery disease, valvular heart disease and/or surgery, CABG, pacemaker, pre-existing heart failure, history of cardiac surgery
		- Physical examination	*Common signs:*
			Anaemic, cyanotic, dyspnoeic, obesity, pulse rate, blood pressure
			*Signs of right heart failure/fluid retention*
			Neck vein distension, increased jugular venous pressure, right ventricular pulsations,
			pulsations of hepar, hepatojugular reflux, hepatomegaly, ascites, leg oedema.
			*Signs of left heart failure/fluid retention*
			Apex palpable, displacement of the apex, pulmonary rales, signs of pleural effusion,
			3rd heart sound, murmurs, tachycardia, irregular heartbeat/ atrial fibrillation
		- ECG	Normal ECG, sinus tachycardia, sinusbradycardia, myocardial infarction, atrial fibrillation, ventricular
			arrhythmia, pathological Q’s, AV-block, micro voltage, QRS > 120 ms or LBTB morphology,
			left ventricular hypertrophy, left bundle branch block, right ventricular hypertrophy
		- Cardiac marker	NT-pro BNP
		- Echocardiography	LV ejection fraction, LV function, end-diastolic diameter, end-systolic diameter, fractional shortening,
			left atrial size, left ventricular wall thickness, valvular structure and function, right ventricular
			hypertrophy, right ventricular dysfunction
		- Data medical record	Blood test, X-thorax
Treatment of heart failure		Medication description	Cardiac medication
		Non pharmacological	Sodium restriction, fluid restriction, supplementary nutrition, physical activity, stop smoking
Cardiovascular risk profile		Cardiovascular risk factors	Smoking, BMI, diabetes mellitus, hypertension, hypercholesterolaemia
Pre-existing heart failure		Data medical record	Specialist that diagnosed heart failure, criteria/ examinations used for diagnoses
Quality of life		Qualidem for psychogeriatric residents	
		SF-12 for somatic residents	
		VAS for somatic residents	
Care dependency		Care dependency scale	

### Demographic data and clinical characteristics

Data regarding general and specific resident characteristics will be gathered for all participants. The variables age, gender, medication, diagnosis on admission and co-morbidity will be retrieved from the medical records. The cognitive status of each resident will be measured using the Mini Mental State Examination (MMSE). This is a valid test of cognitive function including the areas of orientation, registration, attention and calculation, recall, language repetition and complex commands [22].

### Heart failure

#### Physical examination and clinical history

The actual history and physical examination will be recorded on a client record file developed for this study. In somatic residents the history-related questions will be answered by the residents themselves; in psychogeriatric residents these questions will be answered by the nurses responsible for their daily care and/or the family caregiver of the resident.

#### Electrocardiogram (ECG)

The clinical assessment will also include a standard 12-lead ECG, recorded by the research nurse. Abnormal ECG findings will be identified according to predefined criteria.

#### Measurement of N-terminal pro brain natriuretic peptide (NT-pro BNP)

A venous blood sample will be taken to determine the NT-pro BNP concentration. These samples will be analysed in the clinical chemistry laboratory of the Maastricht University Medical Centre on an Elecsys 2010 (Roche Diagnostics, Mannheim, Germany), using the NT-pro BNP assay. A normal concentration of NT- pro BNP <125 pg/ml in an untreated patient has a high negative predictive value for HF [23].

#### Echocardiogram

The echocardiogram will be recorded using a Philips CX50 CompactXtreme Ultrasound System. The echocardiogram will provide essential information about the aetiology and severity of HF.

#### Complementary information from medical records

Additional information will be obtained from the medical records such as main diagnosis on admission, co-morbidity, results of recent blood tests or X-thorax (if available) and currently prescribed medication.

If HF has already been diagnosed, we will search for information in the medical record about who diagnosed HF and on which criteria the diagnosis was based.

### Current treatment of heart failure

To study the current pharmacological treatment of HF in nursing homes data will be collected on cardiac medication prescriptions and data on non-pharmacological treatment will be extracted from the medical and nursing records.

### Care dependency and quality of life

Care dependency will be assessed using the Care Dependency Scale (CDS). The CDS consists of 15 items measuring human needs on a five-point Likert-type scale and the score ranges from 15 (completely dependent on care) to 75 (almost independent of care) [24,25].

Quality of life will be measured using the Short-Form Health Survey 12 item (SF-12) and the Visual Analogue Scale (VAS) for somatic residents. The SF-12 is a short form derived from the SF 36. It has proven validity and it is appropriate for use in studies with a large sample size and studies focusing on patient-based assessments [26]. The visual analogue scale (VAS) subjectively measures the quality of life experienced on a scale from 0–10.

The Qualidem will be used to measure the quality of life in psychogeriatric residents. This scale contains 37 items divided into 9 subscales. It has sufficient validity to be used for research in residential care settings [27,28].

### Statistical analysis

The data will be analysed using SPSS software PASW Statistics 17 and will include descriptive frequency distributions for all variables. Differences between groups will be tested using Student’s T-test or analysis of variance (ANOVA) for continuous (dependent) variables and the Chi-square test (cross-table analysis) and/or multivariable logistic regression analyses for discrete (dependent) variables.

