### Study population and sample

The study population will consist of nursing home residents who receive long term care on somatic or psychogeriatric wards. Both somatic and psychogeriatric residents will be eligible when over 65 years of age. Residents receiving palliative care or admitted for short-term rehabilitation ( staying < 2 months) will be excluded. The overall number of nursing home residents at the five participating healthcare organisations is about 4500. After excluding the places allocated for rehabilitation and terminal care about 3500 residents will be available for recruitment.

A total of 1000 nursing home residents will be included in the study, with 200 from each participating organisation. Based on the current segmentation of somatic residents (35%) versus psychogeriatric (65%) residents in Dutch nursing homes, we aim to include 70 somatic and 130 psychogeriatric residents from each organisation.

In a feasibility study on somatic wards, we found that about 50% of the approached residents were willing to participate. Reasons given for not participating included: they considered themselves too old, or believed that the investigations would be too burdensome. We also encountered difficulties, when asking legal representatives to make decisions regarding participation on behalf of residents. These preliminary findings were in line with a study conducted by Barnes et al, who also focused on the recruitment of older people in a HF study, in which only 30% of the initially identified participants agreed to participate [21].

Therefore, it will probably be necessary to approach three times the number of residents per healthcare organisation in order to recruit 200 residents per site.

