#### Sample size calculation

The calculation of sample size was based on an estimated prevalence of HF in nursing home residents of *p* = 0.20 with a standard deviation of 0.025 and a confidence level (%) of 95%. No power considerations are required, because there is no null hypothesis to be tested. Accordingly, 983 residents should be included in the study; therefore a sample of 1000 residents will be selected.

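### The named tests for care dependency and quality of life assume equal variances although the expected heart failure groups are unequal in size; Welch versions would be a minor, nearly free improvement

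*Protocol article*

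**What the plan says.** The Statistical analysis section tests differences between groups by Student's "T-test or analysis of variance (ANOVA) for continuous (dependent) variables". It names no unequal-variance version and does not say which groups each test compares. It does not mention confidence intervals for these comparisons.

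The group sizes have to be inferred from other sections:

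- Sample size calculation bases the study on "an estimated prevalence of HF in nursing home residents" of "0.20 with a standard deviation of 0.025 and a confidence level (%) of 95" percent, and concludes that "983 residents should be included in the study; therefore a sample of 1000 residents will be selected".
- Study population and sample gives the strata: "we aim to include 70 somatic and 130 psychogeriatric residents from each organisation". With five organisations this makes 350 somatic and 650 psychogeriatric residents. Quality of life is measured with different instruments in the two strata.
- Diagnosis of heart failure sets out three categories (no HF, newly found HF, known HF): "At the end of the assessment all residents will be categorized in one of the following groups".

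For care dependency, "the score ranges from 15 (completely dependent on care) to 75 (almost independent of care"). The VAS for quality of life is also bounded, from 0 to 10. No SD is given for any of these scales.

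**The concern.** Student's t-test and classical ANOVA estimate one common variance. With equal group sizes and two groups this does little harm even if the variances differ. With unequal sizes the pooled variance is dominated by the larger group, here residents without HF, so the standard error is wrong whenever the smaller group has a different spread. If the HF group varies more, the test rejects too often. If it varies less, the test rejects too rarely.

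At the planning prevalence the groups would be about 1 to 4. The comparisons answer research question 3, on the association of HF with care dependency and quality of life. The reliability of the p-values for that question is at stake. This is separate from confounding.

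**Working it through.** **Sample size, reproduced.** n = z²p(1−p)/d² = 1.96² × 0.20 × 0.80 / 0.025² = 983.4, which agrees with the protocol's 983. The 0.025 therefore acts as the half-width of the 95% interval; read as a standard error it would give 0.16/0.025² = 256.

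**Expected group sizes.** 20% of 1000 gives 200 with HF and 800 without. If the same 20% is assumed in each stratum, the comparisons are 70 v 280 (somatic) and 130 v 520 (psychogeriatric). At 25%, the upper end of the Background's range, they are 250 v 750. At 45%, from the Discussion, they are 450 v 550.

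**Two-group test.** Let the SD be r with HF and 1 without, with n₁ with HF and n₂ without. r is an assumption.

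- Pooled variance: s² = [(n₁−1)r² + (n₂−1)]/(n₁+n₂−2)
- Pooled SE = √[s²(1/n₁ + 1/n₂)]; true SE = √(r²/n₁ + 1/n₂)
- q = pooled SE / true SE; true type I error ≈ 2[1 − Φ(t₀.₉₇₅ × q)]

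For r = 1.25 at 200 v 800:

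- s² = (199 × 1.5625 + 799)/998 = 1.1122
- pooled SE = √(1.1122 × 0.00625) = 0.0834
- true SE = √(0.0078125 + 0.00125) = 0.0952
- q = 0.876; 1.9623 × 0.876 = 1.719; type I error = 8.6%

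For r = 0.8:

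- s² = 0.9282; pooled SE = 0.0762; true SE = √(0.0032 + 0.00125) = 0.0667
- q = 1.142; 1.9623 × 1.142 = 2.241; type I error = 2.5%

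True type I error at nominal 5%:

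| SD ratio HF/no HF | 200 v 800 | 250 v 750 | 450 v 550 |
|---|---|---|---|
| 0.67 | 1.3% | 1.7% | 4.2% |
| 0.8 | 2.5% | 2.8% | 4.5% |
| 1 | 5.0% | 5.0% | 5.0% |
| 1.25 | 8.6% | 7.9% | 5.5% |
| 1.5 | 12.1% | 10.6% | 5.9% |

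At 70 v 280 and 130 v 520, q is 0.876 for r = 1.25 and 1.142 for r = 0.8, as at 200 v 800. In large samples q depends only on the ratio of the group sizes and on r, so more residents do not help.

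**Three-group ANOVA.** Simulation with normal data, 20,000 runs, HF split evenly (an assumption). At 800/100/100 with both HF groups at SD ratio 0.8, 1 or 1.25, the classical test rejects in about 1.7%, 4.8% and 10.8% of runs.

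**After the change.** Welch's t-test in simulation rejects in 4.7% to 5.4% of runs at 200 v 800, 70 v 280 and 130 v 520 for ratios 0.67 to 1.5. With equal variances its power against Student's test is 79.5% v 79.5% at 200 v 800 and 79.1% v 79.6% at 70 v 280.

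**The case against.** The strongest reply is that the harm needs unequal variances, and the protocol offers no evidence of them. This stands: unequal group sizes alone do no damage, as the 5.0% row shows.

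Nor can unequal variances simply be inferred from the bounded scales. That argument works through a difference in means, one group sitting nearer a limit. It creates no variance difference when the means are equal, which is where type I error is defined. When the means do differ, the effect is usually modest. As an illustration, assume that variance is proportional to m(1−m), with m the mean rescaled to 0–1. On the CDS, m = 0.5 without HF and 0.4 with HF (0.1 × 60 = 6 points apart) gives an SD ratio of √(0.24/0.25) = 0.98. A less favourable case, 0.2 without HF and 0.3 with, gives √(0.21/0.16) = 1.15 and coverage of about 93% for a pooled 95% interval. A reader might take the 12.1% in the table as the likely error; the documents do not support a ratio as large as 1.5.

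The 1 to 4 split is also not a design feature. HF status is observed in a cross-sectional study, and 20% is an assumption for the precision of the prevalence. The Discussion cites 45% in the one study with focused clinical assessment, the approach adopted here. At that prevalence the two-group problem almost disappears. The three-group ANOVA is less well protected: at 550/225/225 with an SD ratio of 1.25 in both HF groups, simulation gives about 7.4%.

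A final objection is that a condensed article may leave the version of a test to the full plan. Variance checks may indeed be left there. But the article does not stay silent on the test: it names Student's version, so the comment addresses a stated choice.

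**Conclusion.** The point holds as a minor, conditional one. The named tests pool the variance, and the protocol's own planning prevalence implies unequal groups. If the spread differs by HF status, the p-values are then off in a direction that cannot be known in advance. For moderate assumed SD ratios of 0.8 to 1.25 at 200 v 800, the true error lies between about 2.5% and 8.6%. At 450 v 550 it stays within 1 percentage point of 5% over the whole range 0.67 to 1.5. All of these figures rest on assumed SD ratios, and the two-group figures also on a large-sample approximation that simulation confirmed at the 20% group sizes.

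A reader might go further and infer that the planned analysis is invalid, or that planned confidence intervals for research question 3 are mis-sized. The documents support neither. They contain no SDs, and the Statistical analysis section plans no such intervals. Any that are reported from the pooled methods would carry the same conditional error as the p-values.

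**What to change.** In the Statistical analysis section, replace Student's t-test and classical ANOVA with Welch's t-test and Welch's ANOVA. If the comparisons are run as regressions, use heteroscedasticity-robust standard errors instead. State that any confidence intervals reported for the mean differences use the same version.

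This takes one sentence and no additional data. If the variances turn out equal, the power lost with Welch's t-test is at most about 0.5 percentage points in the simulated cases.
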